### Study Outcomes

Outcome measures were collected at 6 time points: before treatments, after washout period, and after 3 and 6 months of treatments (Table 1).

Only one person conducted clinical assessments of participants, and she was blinded to groups to minimize any assessor effects. Biochemical measurements were performed by an expert laboratory technician under the supervision of a laboratory sciences specialist.

In this trial, the primary outcomes were free androgen index (FAI) and homeostasis model assessment–insulin resistance (HOMA-IR). Secondary outcomes were modified Ferriman-Gallwey score (FG); acne; regularity of menstrual cycles; blood pressure; androgenic profiles including follicle-stimulating hormone (FSH), luteinizing hormone (LH), total testosterone (tT), SHBG, androstendione (A4), and dehydroepiandrosterone sulfate (DHEAS); metabolic profiles including fasting blood sugar (FBS) fasting insulin, HOMA-IR, triglycerides (TG), total cholesterol (TC), high-density lipoprotein cholesterol (HDL-C), low-density lipoprotein cholesterol (LDL-C); and quality of life assessed by Health-Related Quality of Life Questionnaire for Polycystic Ovary Syndrome (PCOSQ-50) [13].

**Table 1 table1:** Schedule of clinical and biochemical assessments.

Item		Baseline 1	At 3rd month of treatment	At 6th month of treatments	Baseline 2 (after washout period)	At 3rd month of treatment	At 6th month of treatment
**Demographic characteristics**		x					
	Age, marital, educational, and occupational status						
**Menstrual history**							
	Age of menarche	x					
	Last menstrual period	x	x	x	x	x	x
	Interval between menstrual cycles	x	x	x	x	x	x
	Amenorrhea history	x					
**Medical and family history**							
	Chief complaints (infertility, hirsutism, menstrual irregularity, acne, alopecia)	x					
	Duration of PCOS^a^ diagnosis	x					
	History of previous treatments	x					
	Hair removal methods	x	x	x	x	x	x
	Past medical history	x					
	Family history	x					
**Anthropometric and blood pressure measurements**							
	Height	x					
	Weight	x	x	x	x	x	x
	Waist circumference	x	x	x	x	x	x
	Hip circumference	x	x	x	x	x	x
	Wrist circumference	x	x	x	x	x	x
	Blood pressure	x	x	x	x	x	x
**Clinical hyperandrogenism symptom assessments**							
	FG^b^ score	x	x	x	x	x	x
	Acne	x	x	x	x	x	x
	Androgenic alopecia	x	x	x	x	x	x
**Laboratory assessments**							
	Hormonal parameters (FSH^c^, LH^d^, tT^e^, FAI^f^, SHBG^g^, A4^h^, DHEAS^i^)	x	x	x	x	x	x
	Metabolic parameters (FBS^j^, fasting insulin, HOMA-IR^k^, TG^l^, TC^m^, LDL-C^n^, HDL-C^o^)	x	x	x	x	x	x
Quality of life		x	x	x	x	x	x
Ultrasound assessment		x					

^a^PCOS: polycystic ovary syndrome.

^b^FG: Ferriman-Gallwey score.

^c^FSH: follicle-stimulating hormone.

^d^LH: luteinizing hormone.

^e^tT: total testosterone.

^f^FAI: free androgen index.

^g^SHBG: sex hormone-binding globulin.

^h^A4: androstenedione.

^i^DHEAS: dehydroepiandrosterone sulfate.

^j^FBS: fasting blood sugar.

^k^HOMA-IR: homeostatic model assessment–insulin resistance.

^l^TG: triglycerides.

^m^TC: total cholesterol.

^n^LDL-C: low-density lipoprotein cholesterol.

^o^HDL-C: high-density lipoprotein cholesterol.

### Clinical Assessment

In this study, a single trained midwife in the endocrinology clinic under supervision of a reproductive endocrinologist assessed the anthropometric parameters, menstrual cycles, hirsutism, acne, alopecia, and acanthosis nigricans in participants at baselines and follow-ups. She was blinded to type of treatment.

Patient weights were measured when they were minimally clothed using a digital scale (Seca 707, Seca GmbH) and rounded to the nearest 100 grams. Height was measured without shoes in the standing position with shoulders in normal alignment using a tape measure. Waist circumference was measured with an unstretched tape measure at the level of umbilicus without any pressure to the body surface and recorded to the nearest 0.1 cm. Hip circumference was measured at the level of anterior superior iliac spine without any pressure to the body surface. Wrist circumstance was measured similarly. Body mass index was calculated as weight in kilograms (kg) divided by height squared (m^2^). Systolic and diastolic blood pressure were measured twice on the right arm with the patient in a seated position by a qualified midwife with a standard mercury sphygmomanometer after the subject sat for 15 minutes; the mean of these 2 measurements was recorded.

All patients were evaluated for regularity of menstrual cycles. Those who had intervals of menstrual cycle more than 35 days were diagnosed as having oligomenorrhea, less than 22 days as polymenorrhea, and those with absence of menstrual periods for 6 months or longer as amenorrhea [37,38]. Spotting was assessed and registered.

In this study, the FG score was used for determining the density of terminal hair at 9 different body sites: upper lip, chin, chest, upper back, lower back, upper abdomen, lower abdomen, arm, and thigh; this scoring system grades excess terminal body or facial hair growth based on a scale of 0 (absence of terminal hairs) to 4 (frank virilization), and a total score of 8 or more is considered as hirsutism [39,40]. Participants were asked to refrain from shaving or using other depilatory methods in the month before evaluation to improve accuracy of assessment.

The severity of acne was classified according to a grading system based on the number of lesions and their spread on the face, back, and chest: mild—comedones (clogged hair follicles often similar to pustules that do not have any inflammation) present; moderate—the number of erythematous and popular moderate lesions was from 10 to 40 or number of pustules was from 10 to 40 (especially on the face); moderate to severe—the number of multiple and numerous papules and pustules was from 40 to 100 often accompanied by comedones in numbers of 40 to 100 on the face, upper chest, and back; severe—nodulocystic acne with painful nodules or pustules frequently observed on the chest and face and accompanied by smaller papules, pustules, and comedones [41].

To diagnose androgenic alopecia in participants, we used the following classification, which was presented by Ludwig [42] in Germany:

Grade I: perceptible thinning of the hair on the crown limited in the front by a line situated 1 to 3 cm behind the frontal hair lineGrade II: pronounced rarefaction of the hair on the crown within the area seen in Grade IGrade III: complete baldness (total denudation) within the area seen in Grades I and II

In addition, we will assess the common side effects of OCs during and after follow-ups (Table 2).

### Hormonal Assay

FSH and LH will be measured by immunoradimetric assay (IRMA) (Institute of Isotopes Co Ltd) using the Wallac Wizard gamma counter (GMI Inc); tT, A4, and DHEAS will be measured by enzyme immunoassay (EIA) (Diagnostics Biochem Canada Inc). SHBG will be measured by immunoenzymometric assay (IEMA) (Mercodia AB); all enzyme-linked immunosorbent assay (ELISA) tests were performed using the Sunrise ELISA reader (Tecan Trading AG); and FAI will be calculated using the formula [tT(nmol/L)×100/SHBG(nmol/L)].

Biochemical hyperandrogenemia will be identified if FAI, DHEAS, or A4 levels are in the upper 95th percentile (tT=0.89 ng/mL, A4=2.9 ng/mL, DHEAS=179 μg/dL, FAI=5.39) considering the women studied were not on any hormonal medication and had no clinical evidence of hyperandrogenism and menstrual dysfunction. Hyperandrogenism was determined as clinical hyperandrogenism and/or biochemical hyperandrogenemia [43].

Inter- and intra-assay coefficients of variation for all hormonal measurements will be defined.

**Table 2 table2:** A comparison of the common side effects of oral contraceptives in polycystic ovary syndrome patients.

Side effects	Type of treatment			
	OC^a^ containing LNG^b^	OC containing CA^c^	OC containing DRSP^d^	OC containing DSG^e^
Headache	x	x	x	x
Dizziness	x	x	x	x
Nausea	x	x	x	x
Vomiting	x	x	x	x
Breast pain/tenderness	x	x	x	x
Spotting	x	x	x	x

^a^OC: oral contraceptive.

^b^LNG: levonorgestrel.

^c^CA: cyproterone.

^d^DRSP: drospirenone.

^e^DSG: desogestrel.

### Metabolic Assessment

FBS will be measured using the glucose oxidase method (Pars Azmun Co). HOMA-IR will be calculated using electrochemiluminescent immunoassay (ECLIA). Normal range of HOMA-IR is determined in the Iranian population by using ECLIA method with a cut-off of 2.63 [44]. TG levels will be measured using the enzymatic colorimetric method with glycerol phosphate oxidase (Pars Azmun Co). TC level will be determined using enzymatic colorimetric method with cholesterol esterase and cholesterol oxidase (Pars Azmun Co). Level of HDL-C will be determined after precipitation of apolipoprotein β with phosphotungstic acid and enzymatic colorimetric method (Pars Azmun Co). LDL-C level will be calculated using enzymatic colorimetric method (Pars Azmun Co) [45]. Serum insulin concentration will be measured using ECLIA method (Roche Diagnostics) [46]. Albumin will be measured using the enzymatic colorimetric method with cholesterol esterase and cholesterol oxidase (Pars Azmun Co). Inter- and intra-assay coefficients of variation for all metabolic measurement will be defined.

### Ultrasound Assessment

Ultrasound examination of the uterus and ovaries was performed using a 6-MHz transvaginal transducer or a 4-MHz transabdominal transducer in cases where sociocultural constraints precluded a vaginal approach for ultrasonography. Sonography was performed at the first baseline visit when the blood samples were collected. Endometrial thickness, ovarian volume, number, diameter, and distribution of the follicles were recorded. The ovaries were considered as polycystic when observed as having increased ovarian size and/or at least 10 follicular cysts measuring 2 to 9 mm [47].

### Quality of Life Assessment

The PCOSQ-50, developed by Nasiri-Amiri et al [13], was used to evaluate the quality of life of recruited participants. This questionnaire includes 50 items in the following 6 domains: psychosocial and emotional, fertility, sexual function, obesity and menstrual disorders, and coping. Items were scored based on the 5-point Likert scale.

### Sample Size

To show that the OCs containing LNG are clinically as effective as those containing antiandrogenic progestins including DRSP, CA, EE, and DSG, we used a noninferiority hypothesis as seen in Figure 3, where μ_T_ is the mean of the test drug, μ_S_ is the mean of standard therapy, and δ is a difference of clinical importance. By rejecting the null hypothesis, we conclude that the difference between the test drug and the standard therapy is less than a clinically meaningful difference (ie, δ), and therefore the test drug is as effective as the standard therapy [48].

We considered 80% power, 0.05 type I error, and ϴ=0.52, where ϴ is defined as the difference of mean of test drug and standard therapy minus difference of clinical importance divided by standard division, as seen in Figure 4. Sample size was calculated from the table introduced by sample size calculations in clinical research, as seen in Figure 5 [49].

We estimated 25 samples were needed for each group, with 150 total samples needed. Considering 25% withdrawal, we will need 200 cases.

### Randomization and Blinding

A blocking or stratification random allocation with a block size of 6 using a computer-based random number generator was prepared to assign participants to treatment groups. The randomization sequence was prepared before the trial, initiated by an independent statistician. For those patients meeting the inclusion criteria and providing informed consent, the research assistant assigned the next randomization sequence according to the schedule. Although participants couldn’t be blinded to treatment type because the artifact was obvious, both clinical examiner and data analyst were blinded to participant groups during the trial.

**Figure 3 figure3:**

Noninferiority hypothesis.

**Figure 4 figure4:**

Standardized difference of observational and clinical mean difference.

**Figure 5 figure5:**

Sample size formula.

### Statistical Analysis

Descriptive statistics will be reported appropriately; normality assumptions will be tested per case by Kolmogorov-Smirnov or Shapiro-Wilk tests. A crossover study is a longitudinal study type in which participants receive treatments in different phases. Therefore, we will use repeated measures which are correlated. We will use statistical analysis appropriate for correlated measures such as generalized estimated equations or repeated-measurement designs to find the differences between treatments. This will be done after finishing the second phase. In addition, in first phase of study, we will estimate between-group differences using generalized linear models. A washout period was taken into account although carryover effect (residual effect) will be tested at the beginning of the analysis via appropriate statistical tests like *t* tests presented by Fleiss [50]. Statistical analysis will be performed using the software package Stata version 12 (StataCorp LLC).

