Several studies that assessed the effectiveness of OCs on clinical, biochemical, and metabolic profiles in PCOS patients have reported conflicting findings [1,10,15,16,32-35]. However, a limited number of studies have compared the effects of the various OC products on different aspects of PCOS; the majority of these studies did not assess effects of OCs containing LNG.

Accordingly, in this crossover randomized controlled clinical trial, we aimed to compare the effects of OCs containing LNG with products containing antiandrogenic progestins on the clinical, hormonal, and metabolic aspects and quality of life of reproductive-age women with PCOS.

We hypothesize that in PCOS patients, OCs containing antiandrogenic progestins including DRSP, CA, and DSG have no advantage over products containing LNG on the clinical, hormonal, and metabolic profiles of these women or on their quality of life.

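### The sample size rests on a noninferiority hypothesis for LNG, but the stated analysis only looks for differences, and the margin has no value for FAI or HOMA-IR

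*Protocol article*

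**What the plan says.** The Introduction hypothesises that the antiandrogenic products "have no advantage over products containing LNG on the clinical, hormonal, and metabolic profiles of these women". The Sample Size section makes this a noninferiority aim: "To show that the OCs containing LNG are clinically as effective as those containing antiandrogenic progestins", for which "we used a noninferiority hypothesis". It also gives the decision rule. On rejecting the null, "we conclude that the difference between the test drug and the standard therapy is less than a clinically meaningful difference".

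The margin is described only in words: "δ is a difference of clinical importance". The planning values are "We considered 80% power, 0.05 type I error" and ϴ=0.52, which is "defined as the difference of mean of test drug and standard therapy minus difference of clinical importance divided by standard division". The result is 25 women per group, 150 in all, and 200 after allowing for 25% withdrawal.

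The Study Outcomes section names two primary outcomes, FAI and HOMA-IR. The Statistical Analysis section then gives this purpose for the crossover analysis: "We will use statistical analysis appropriate for correlated measures such as generalized estimated equations or repeated-measurement designs to find the differences between treatments". It adds generalized linear models to estimate between-group differences in the first phase. It mentions no margin, no noninferiority test and no confidence limit.

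Two other places matter. The Interventions section labels the LNG product the standard therapy. The Discussion would recommend LNG as a cost-effective first-line option if it proves equally effective without safety concerns.

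**The concern.** The question used to size the trial and the question described for the analysis are different. A noninferiority claim needs the confidence interval for LNG minus comparator to exclude a harm as large as δ. A difference analysis asks whether the interval excludes zero. Failing to exclude zero does not establish that LNG is as effective, and excluding zero does not establish that the difference matters clinically.

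Even a reader who wants to apply the Sample Size rule cannot do so. δ has no number in FAI or HOMA-IR units, and it cannot be recovered from ϴ. The label given to LNG adds doubt about which product is test and which is reference, and so about which confidence limit is compared with the margin. At stake is the trial's main conclusion: as written, the analysis does not lead to the recommendation that the Discussion envisages. A margin chosen after the data are seen would carry little weight.

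**Working it through.** **Inputs from the protocol article.** Type I error 0.05 (sidedness not stated), power 80%, ϴ=0.52, 25 per group (Sample Size). Each comparator occupies two of the six groups, one per treatment order (Interventions), so a crossover comparison has 2 × 25 = 50 women.

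**Assumptions, not in the document.** The planning difference is 0, so in size δ = 0.52 SD. The difference test is two-sided at 5%. For paired figures the SD is that of within-woman differences; for the first-phase figure it is the between-woman SD.

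**1. Reproducing the stated sample size.**
- Normal formula, one-sided 0.05: (1.645 + 0.842)² / 0.52² = 22.9, so 23.
- One-sample t test, one-sided 0.05 (noncentral t): power is 0.796 at n=24 and 0.811 at n=25, so n=25. This is the stated figure.
- 25 × 6 = 150, and 150 / 0.75 = 200, as stated.
- Variants that do not give 25: one-sample t at one-sided 0.025 gives 32; a parallel comparison at one-sided 0.05 gives 47 per arm by t.

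The sample size is therefore consistent with a one-sided noninferiority calculation at 0.05. It is not in dispute.

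**2. What ϴ says about δ.** δ = 0.52 × SD. For assumed SDs of 1, 2 and 4 units, δ is 0.52, 1.04 and 2.08 units. If the planning difference was not 0, δ cannot be recovered even with the SD known.

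**3. Difference test when LNG is worse by exactly δ.** The noncentrality is 0.52√n for n pairs and 0.52√(n/2) for n per arm. The chance of non-significance is the noncentral t probability between ± the critical value.

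| Comparison | Noncentrality | Critical t (df) | Non-significant |
|---|---|---|---|
| 50 pairs | 0.52√50 = 3.68 | 2.011 (48) | 5% |
| 25 pairs | 0.52√25 = 2.60 | 2.064 (24) | 30% |
| First phase, 25 v 25 | 0.52√12.5 = 1.84 | 2.011 (48) | 56% |

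A one-sided 5% noninferiority test passes in 5% of trials in every row, by construction.

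**4. Half the margin, 50 pairs.** The noncentrality is 0.26√50 = 1.84, the same as in the last row, so the difference is significant in 1 − 0.56 = 44% of trials. Such a result could be misread as failure although the true difference lies inside the margin.

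**5. The two rules side by side, in SD units of the observed difference.** Significance needs more than t(0.975)/√n; noninferiority needs less than 0.52 − t(0.95)/√n (√(n/2) for 25 v 25).
- 50 pairs: 2.011/7.071 = 0.284, and 0.52 − 1.677/7.071 = 0.283.
- 25 pairs: 2.064/5 = 0.413, and 0.52 − 1.711/5 = 0.178.
- 25 v 25: 2.011/3.536 = 0.569, and 0.52 − 1.677/3.536 = 0.046.

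With 50 pairs the two cut-offs almost coincide. Under these assumptions the 44% is therefore close to the rate at which a noninferiority test would itself fall short; it is not an added error. With 25 pairs, observed differences from 0.178 to 0.413 SD are non-significant yet not noninferior. In the first phase that gap runs from 0.046 to 0.569 SD.

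**The case against.** The strongest reply is that the Sample Size section already states a noninferiority rejection rule, and that the analysis section names models rather than a significance test. It gives no null of no difference and no P value threshold for the treatment effect. A GEE or repeated-measures estimate with its interval is what a noninferiority comparison would use. This stands: the models fit the purpose, and what is missing is the link to δ.

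A reader might infer that a non-significant result will be reported as no advantage. The document does not say so. The wording of the hypothesis and of the analysis leaves that reading open, but the Sample Size rule points the other way.

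A reader might also infer a large inflation of false noninferiority claims in the main analysis. That is not supported. With 50 pairs and a within-woman SD, the 30% falls to 5%, and the 56% belongs to the supplementary first-phase analysis under a between-woman SD. Nor is one ϴ for two outcomes an error in itself, since ϴ is dimensionless and can size both.

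Finally, this is a condensed article. Details of the test may sit in an analysis plan or full protocol that is not shown, and the content of Figures 3 to 5 is not visible. Their captions describe a hypothesis, a standardized difference and a formula, so a value for δ there is unlikely but cannot be excluded. Yet the article prints the error rate, power, ϴ and sample size without the margin beneath them, and states an analysis purpose that does not match. That is a mismatch within the document, not only an omission.

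**Conclusion.** The point holds. The trial is sized for noninferiority of LNG, the described analysis finds or estimates differences without carrying over the noninferiority rule, and the visible text gives δ no value for FAI or HOMA-IR. As written, the plan does not answer its own question.

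The numerical consequence depends on which SD lies behind ϴ and on how many women enter each comparison. With LNG worse by exactly δ, non-significance ranges from 5% (50 pairs) through 30% (25 pairs) to 56% (first phase). All three figures assume a planning difference of 0 and a two-sided 5% difference test. With 50 pairs, the near agreement between non-significance and noninferiority is a coincidence of that sample size and SD. It is no reason to leave the rule unstated. The stated sample size is not at fault.

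**What to change.** In the Statistical Analysis section, state that for each comparator the LNG-minus-comparator difference from the crossover model will be compared with δ. Noninferiority is declared only if the one-sided 95% upper confidence limit lies below δ, higher FAI and HOMA-IR being worse. The 95% level matches the one-sided 0.05 that reproduces 25 per group; the sidedness should be written down.

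Name LNG as the test drug in the hypothesis and reconcile this with the label in the Interventions section.

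Before the data are analysed, record:
- δ in FAI units and in HOMA-IR units;
- the assumed difference and the SD behind ϴ=0.52, and whether that SD is within- or between-woman;
- the primary time point.

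The cost is wording plus writing down planning values that must have been used to obtain ϴ. The model and sample size need not change, and no new data are needed. By the article's own account, follow-up is still under way and analysis comes after completion, so there is time to do this before the data are analysed.

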## Results

This trial began enrollment in February 2016, and 200 participants are currently enrolled as planned. Recruitment of participants and follow-ups are still ongoing, and preliminary results are expected to be published in 2018.

## Discussion

This study presents a protocol for a crossover randomized controlled trial to compare the effects of OCs containing LNG with products containing antiandrogenic progestins including CA, DRSP, EE, and DSG on clinical, hormonal, and metabolic findings and quality of life of reproductive-age women with PCOS. To our knowledge, this is the first trial with crossover design to compare the effects of different OCs on various clinical and biochemical aspects of PCOS. Results of this study will empower clinicians with evidence-based recommendations regarding treatment options and follow-up duration.

Different approaches have been used to treat patients with PCOS. Use of OCs is one of the most common treatment options for improving clinical and biochemical findings of PCOS [21,51]. It is well known that improvement in clinical signs of PCOS usually begins after 3 to 6 months of therapy, but because hair follicles have a half-life of up to 6 months, lifelong therapy may be needed to prevent recurrence [16,52]. In this study, patients were treated with OCs for a 6-month period in each phase.

To minimize selection bias, we enrolled patients from different settings such as professional social networks and municipal health centers, private clinics, and from among participants of the TLGS. These settings were located in different districts of Tehran. All patients who met the eligibility criteria were included in the study. Adolescent and premenopausal patients were not included in the trial because of different clinical and hormonal statuses in these periods.

An important strength of this study is its crossover design, in which the interventions under investigation are evaluated within the same patients, eliminating between-subject variability [53]. We designed this study and its methodological issues such as allocation, blinding, flow diagrams, patient preference, and carryover effects based on guidelines reported in the CONSORT statement [36]. This clinical trial is a head-to-head trial that permits patients to receive multiple treatments; hence, it can express preferences for or against particular treatments.

This study has limitations. Patients may drop out after the first intervention period and not receive a second treatment. This makes within-subject comparison impossible and is particularly important if withdrawal is related to side effects. We expect a considerable rate of loss to follow-up. To eliminate carryover effects, a washout period of 6 to 8 weeks was scheduled between treatments. Considering carryover effects of treatments across study periods can potentially distort the results obtained during the second treatment and the observed treatment effects will depend upon the order in which they will be received, hence we designed 6 treatment arms with different treatment orders. We intend to assess side effects of treatments. Considering our patients were diagnosed by AES criteria, our results may not be generalizable for those minor phenotypes diagnosed using Rotterdam criteria.

Finally, it is important to note that this project and its design are novel in the management of PCOS. If OCs containing LNG are as effective as OCs containing CA, DRSP, EE, or DSG without safety concerns, they may be recommended as a cost-effective first-line treatment for patients who suffer from the symptoms of PCOS. Therefore, we predict that the findings of this clinical trial will provide useful information for clinicians.

